### Procedure for unblinding if needed {17b}

Blinding may be lifted after completion of the last outpatient follow-up visit (FU4), or in case of any serious adverse event that is probably related to the study.

## Data collection and management

### Plans for assessment and collection of outcomes {18a}

Preoperative data is collected from the preoperative assessment of the anesthesiologist (medical history, comorbidity, and medication use) and neurosurgeon (surgical indication) available in the electronical patient files. Preoperative patient questionnaires are on paper source documents. Intraoperative data and used materials are collected from the surgical reports filed by the neurosurgeon and ENT. Data from the outpatient follow-up visits and postoperative imaging are available in the electronic files. Postoperative questionnaires are filled out on paper source documents. Data transfer from source documents to the RedCap data collection tool will be done by trained study personnel (research assistant). Regular data quality checks are performed in RedCap to ensure complete and accurate data transfer. Paper source documents will be stored for 10 years after completion of the study in a secure location at the study site.

### Plans to promote participant retention and complete follow-up {18b}

The postoperative follow-up visits are planned and notified to the patient before hospital discharge. If the patient is not present at one of these appointments, or if the clinical follow-up appointment is rescheduled outside the visit time window (+ / − 1 week for FU1 and FU2; + / − 2 weeks for FU3 and FU4), the patient is contacted by telephone to reschedule the visit. If this attempt is unsuccessful, the patient is considered lost to follow-up. In case of subject withdrawal, an exit note is added to the electronic Case Report Form (e-CRF) mentioning the withdrawal date and reason of withdrawal.

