### Criteria for discontinuing or modifying interventions {11b}

After allocation to the experimental or control arm, several circumstances—specified as perioperative exclusion criteria- can still lead to excluding the patient from the study. A patient allocated to the control arm may be excluded in case of a clear indication for a hypersensitivity reaction to commercially available fibrin sealants. Patients allocated to L-PRF treatment may be excluded if the L-PRF preparation process fails or if the product is considered of insufficient quality. In case the surgeon identifies other intraoperative findings that may constrain the conduct of the study procedure the subject can be excluded as well, to ensure optimal patient care in that situation. For example, when the damage to the dura is exceptional, the surgeon may opt for a multilayer reconstruction using multiple grafts, commercially available sealants, and autologous materials. Furthermore, study participants can withdraw from the study at any moment, implying that all subsequent study procedures and data collection are discontinued.

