#### Outpatient follow-up

The patient is seen at the outpatient clinic at four occasions to evaluate the postoperative status: after 2 weeks, 4 weeks, 3 months, and 1 year. At each of these visits, a nasal endoscopy is performed to evaluate healing using the Ohio State University crusting scale from 0 to 3 (Table 3). Signs and symptoms of CSF leakage or fistula formation will be recorded. The patient will be asked to complete nasal symptom scoring (SNOT-22, SBI, VAS scoring) and EQ-5D-3L questionnaires to assess the quality of life. At FU3 and FU4, post-operative MR images will be evaluated as well.

**Table 3 Tab3:** Ohio State University crusting scale

Crusting	
0	No crusting
1	Minimal crusting debrided with suction only
2	Moderate crusting (coating) requiring forceps debridement
3	Severe crusting (casting) causing obstruction

FU1 is an additional study visit, which is not part of the standard of care.

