### Methods in analysis to handle protocol non-adherence and any statistical methods to handle missing data {20c}

The results will be analyzed according to the following principles: the “intention-to-treat” (all randomized participants, irrespective of protocol adherence), the “per protocol” (only participants that were treated according to the protocol), and the “as treated” (all participants according to the treatment they received) principles. These three analyses will be compared to show how a lack of data possibly impacts the results. For the primary endpoint, no missing data are expected. For secondary endpoints (cost-effectiveness evaluation), the predictive mean of the other values within the arm will be used.

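### The lost-to-follow-up rule (any one missed or out-of-window visit plus one failed telephone attempt) can leave the 3-month leak status uncollected when it could still be obtained

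*Protocol article*

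**What the plan says.** The section on participant retention {18b} gives the trigger, "If the patient is not present at one of these appointments, or if the clinical follow-up appointment is rescheduled outside the visit time window", and the action, "the patient is contacted by telephone to reschedule the visit". The consequence is "If this attempt is unsuccessful, the patient is considered lost to follow-up". No second attempt, contact with the general practitioner or check of records is named. The label attaches to the patient, not to the visit.

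The rule covers all four outpatient visits. The 2-week visit is among them, although the outpatient follow-up section notes that "FU1 is an additional study visit, which is not part of the standard of care".

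On withdrawal, section {11b} says that "study participants can withdraw from the study at any moment, implying that all subsequent study procedures and data collection are discontinued".

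The primary endpoint (Outcomes {12}) is success at 3 months, meaning no CSF leak that requires revision surgery or another intervention such as lumbar drainage, repeat imaging or a longer stay. Data management {19} describes the comparison as leakage within 3 months of surgery. For sources, section {18a} states: "Data from the outpatient follow-up visits and postoperative imaging are available in the electronic files".

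Section {20c} defines the intention-to-treat analysis as covering everyone randomized and adds: "For the primary endpoint, no missing data are expected". It gives no rule for a patient whose 3-month status is unknown.

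**The concern.** The primary endpoint is an event with clinical consequences, and such events usually leave a trace outside a study visit. Missing the 2- or 4-week appointment is therefore no reason for the 3-month status to be unknown. The retention rule nevertheless closes the patient's follow-up after one failed call, and does not say whether leak status is still sought.

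Patients who are readmitted or treated elsewhere for a leak are plausible non-attenders. If leaks go unrecorded more often than successes, in equal proportion in both arms, both failure rates and their difference shrink. In a non-inferiority comparison that favours a claim of non-inferiority. With few failures expected, a very small number of such patients could matter.

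**Working it through.** **Inputs.** From Sample size {14}: success 94.3% (control) and 95% (L-PRF), margin 0.07, one-sided alpha 0.05, power 80%, 106 per arm needed, 110 per arm enrolled, expected drop-out below 2%. The failure counts in step 3 and the loss rates in steps 4 and 5 are assumptions.

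**1. The plan's own figure.** With unpooled variance,

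n per arm = (1.645 + 0.842)² × (0.943 × 0.057 + 0.95 × 0.05) / (0.95 − 0.943 + 0.07)² = 6.183 × 0.10125 / 0.005929 = 105.6.

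This rounds up to 106 per arm, or 212, as stated. Enrolling 220 covers a loss of 1 − 212/220 = 3.6%.

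**2. Expected failures.** 110 × 0.057 + 110 × 0.050 = 6.3 + 5.5 = 11.8.

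**3. Effect of one leak.** Lower bound = d − 1.645 × √[p_C(1 − p_C)/n_C + p_T(1 − p_T)/n_T], where d is L-PRF success minus control success. Control failures are fixed at 6/110.

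| L-PRF failures | d | SE | Lower bound | Against −0.07 |
|---|---|---|---|---|
| 8/110, all leaks recorded | −0.0182 | 0.0329 | −0.072 | not shown |
| 7/109, one leaker absent from the analysis | −0.0097 | 0.0319 | −0.062 | non-inferior |
| 7/110, one leaker counted as a success | −0.0091 | 0.0318 | −0.061 | non-inferior |

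The statistical methods section {20a} reports a 95% interval. If its two-sided lower limit (multiplier 1.96) were used, the same switch would occur one failure lower: 7/110 gives −0.071 and 6/109 gives −0.061.

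**4. Selective loss, as an illustration.** Take the boundary case: failure rates 12.7% (L-PRF) and 5.7% (control). Suppose a share q of failures in both arms is lost and no success is. The observed rate becomes f(1 − q)/[f(1 − q) + 1 − f]. The type I error is P(Z > 1.645 − (d + 0.07)/SE), with n held at 110.

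| q | Failures lost, of 110 × (0.127 + 0.057) = 20.2 | Observed d | Type I error |
|---|---|---|---|
| 0 | 0 | −0.070 | 5.0% |
| 10% | 2.0 | −0.064 | 6.8% |
| 20% | 4.0 | −0.058 | 9.5% |
| 30% | 6.1 | −0.052 | 13.5% |

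Reducing n for the losses gives 6.8%, 9.5% and 13.4%.

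**5. Random loss.** Power = Φ(0.077/√(0.10125/n) − 1.645). From 110 per arm:

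| Loss | n per arm | Power |
|---|---|---|
| 0% | 110 | 81.4% |
| 2% | 107.8 | 80.7% |
| 5% | 104.5 | 79.6% |
| 10% | 99 | 77.7% |

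**The case against.** A reader might infer that outcomes of patients classed as lost are thrown away. The article does not say so. The retention section applies a label. It does not delete data, forbid reading records, or remove anyone from the analysis. Only withdrawal is said to stop data collection, and the intention-to-treat definition points towards keeping everyone. If leak status is read from the files regardless of attendance, expecting no missing primary data is consistent.

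Other routes would also catch many leaks. A leak that causes or prolongs hospitalization meets the serious adverse event definition in section {22} and must be reported on first knowledge. In-hospital harms are collected from examinations and nursing reports. Hospitalization reports are source documents {19}, and digital follow-up has been possible since March 2020 {3}. Some failures occur before discharge, when no visit can yet have been missed. A patient lost only at the 1-year visit has already passed the endpoint. The full protocol and consent form, which are not shown, may add detail.

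A reader might also take 6.8% to 13.5% as the trial's actual type I error. Those figures require every lost patient to be a leaker whom no other route catches. The numbers lost are small, about 2 to 6 of 220, but nothing in the article supports so selective a pattern.

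All of this stands, and it limits the point. It does not settle what the rule leaves open: whether anyone still looks for the 3-month status once the label is applied. Nor can a leak treated at another hospital be assumed to appear in the site's own record.

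**Conclusion.** The point holds in a limited form. The printed rule closes a patient's follow-up too readily for an endpoint that can largely be established without a visit, and its effect on the primary outcome is unstated. It needs reconciling with the missing-data section.

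The size rests mainly on step 3: about 12 expected failures, and a conclusion that one unrecorded L-PRF leak can reverse. That example is chosen near the margin, and an unrecorded control leak would push the other way. The type I figures only illustrate the direction and possible scale of selective loss. Random loss is minor, and enrolment already covers 3.6%. How many patients will actually be classed as lost is unknown; the plan expects less than 2% drop-out from all causes. This is a worthwhile, inexpensive correction, below the level of a mandatory one.

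**What to change.** Amend the retention and withdrawal sections as follows:

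- A missed or late visit counts only as a missed or late visit. Follow-up continues, and data from late visits are kept with their actual dates.
- A patient is lost for the primary endpoint only if leak status up to 3 months cannot be established from the patient, the general practitioner or hospital records.
- The label removes nobody from the intention-to-treat set.
- A participant who stops study visits may agree to collection of 3-month leak status from records. Without that agreement, collection ends as now.

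The cost is protocol wording, one e-CRF field for the source of the 3-month status, one extra field on the withdrawal form, and a record check for a few patients. The downside is that some statuses will come from records instead of endoscopy; the source field makes these identifiable. Treatment, margin and sample size are unchanged.

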### Data management {19}

Data collection is performed partially on paper source documents (patient questionnaires) and partially on electronic source documents (patient medical records containing surgical and hospitalization reports, registration of used materials). Data are collected by the principal investigator or his designee and locally entered into the e-CRF (RedCap). RedCap is primarily a data collection tool that facilitates post study analysis based on qualitative data. Access to the e-CRF is strictly regulated and only possible after passing a test and with personal credentials. All operations on data are monitored and verified via a tracking system. Entries are verified by double entry (for example manual and automated summary of VAS, SNOT-22, and EQ-5D result), format checks e.g. integer, and warning messages if data are outside an expected range of values.

As appropriate, baseline characteristics will be reported by mean and standard deviation or number and proportions. The effect of the intervention on the primary outcome will be assessed by comparing the proportion of patients presenting with a postoperative CSF leakage within 3 months after surgery.

### Confidentiality {27}

Each patient is identified by a unique study subject number, to ensure the subject’s pseudonymity. All data are processed without identifiable reference to the patient. At each study site one secured identification list is available in the investigator site file. The list contains the code with the study subject number and the patient’s name, birth date, and hospital number.

### Plans for collection, laboratory evaluation, and storage of biological specimens for genetic or molecular analysis in this trial/future use {33}

As referred to in item 26b, no biological specimens will be collected.

## Statistical methods

### Statistical methods for primary and secondary outcomes {20a}

Data will be analyzed in GraphPad Prism software using a simple *t*-test, or nonparametric Mann–Whitney *U* test when not normally distributed, with Bonferroni Holm correction for multiple testing. A *p*-value ˂0.05 is considered statistically significant. The primary outcome, i.e., CSF leakage, will be analyzed in terms of a difference in risk between the two treatment groups. The mean difference between the two treatment groups will be reported as a 95% confidence interval. Secondary endpoints are calculated using simple *t*-test, or nonparametric Mann–Whitney *U* test when not normally distributed, or Fisher’s exact test or chi-squared test, based on the number of events.

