### Sample size {14}

Sample size calculation was performed according to the primary outcome, using an online power calculator for binary outcome non-inferiority trials (Sealed Envelope Ltd. Available from: https://www.sealedenvelope.com). This is a non-inferiority trial with a binary outcome using a one-sided alpha 0.05 and 80% power. The assumed success rate is 94.3% in the control arm, based on center-specific experience as well as the literature [14]. Data on the use of L-PRF for this indication is limited, but we assume a 95% success rate based on prior feasibility studies [8–10].

The statistical hypothesis for testing the treatment difference is presented as follows; H_0_: Δ ≤  − 0.07 tested against the alternative hypothesis H_A_: Δ >  − 0.07, where Δ is the difference between the success rates of experimental and control condition and − 0.07 is the non-inferiority difference. The non-inferiority limit was set at 0.07 considering (a) reported CSF leakage rates without commercially available fibrin sealant averaging 17.2% [15] and (b) important additional benefits of L-PRF compared to commercially available fibrin sealants including the completely autologous nature (eliminating immune reactions), presence of immunologic cells and reduced costs.

Based on this power calculation, 212 patients need to be included, 106 in each group. In order to account for potential missing follow-up information, failure of L-PRF preparation, or non-adherence to the allocation (expected drop-out rate less than 2%), 220 subjects will be enrolled, 110 in each group.

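### The primary analysis section does not turn the −0.07 non-inferiority hypothesis into a decision rule, and its general test sentence and 95% CI do not match the binary outcome or the one-sided 0.05 used for sizing

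*Protocol article*

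**What the plan says.** The Protocol article, Sample size {14}, sets out the design: "This is a non-inferiority trial with a binary outcome using a one-sided alpha 0.05 and 80% power". The null hypothesis is Δ ≤ −0.07, "where Δ is the difference between the success rates of experimental and control condition". On the margin it says "The non-inferiority limit was set at 0.07". The planning rates are "The assumed success rate is 94.3% in the control arm" and, for L-PRF, "we assume a 95% success rate based on prior feasibility studies". This gives 212 patients (106 per arm), raised to 220 (110 per arm).

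Statistical methods for primary and secondary outcomes {20a} begins "Data will be analyzed in GraphPad Prism software using a simple *t*-test, or nonparametric Mann–Whitney *U* test when not normally distributed", adds a Bonferroni–Holm correction, and takes p<0.05 as significant. The primary outcome then has its own provision: "The primary outcome, i.e., CSF leakage, will be analyzed in terms of a difference in risk between the two treatment groups". The difference, called a mean difference, is to be reported with a 95% confidence interval. Fisher's exact and chi-squared tests appear only for secondary endpoints there, and for subset analyses in section {20b}.

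**The concern.** A non-inferiority conclusion needs a stated comparison of a confidence limit, or a shifted test, with the margin. The analysis section has none. Four points do not fit together:

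- **Hypothesis.** The only decision threshold is p<0.05, with no null value and no sidedness. As conventionally run, the tests named test equality, not −0.07.
- **Outcome type.** The opening sentence is general and the section covers the primary outcome. A yes/no outcome is never normally distributed, so the normality switch, read literally, leads to Mann–Whitney, which gives no risk difference. No test for proportions is assigned to the primary outcome.
- **Level.** The lower limit of a 95% CI is a one-sided 0.025 bound. The trial was sized at one-sided 0.05.
- **Direction.** The hypothesis is written for success and the analysis for leakage. That reverses the sign of the difference, and the margin is not restated.

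At stake is the trial's one primary conclusion. The same data could be declared non-inferior or not, depending on which sentence the analyst follows.

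**Working it through.** **Inputs**, all from Sample size {14}: control success 0.943; L-PRF success 0.95; margin 0.07; one-sided alpha 0.05; power 80%; 106 per arm, 110 after allowance for drop-out. Expected failures per arm at 106: 106 × 0.057 = 6.0 (control) and 106 × 0.05 = 5.3 (L-PRF).

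**1. Reproduce the plan's sample size.**
n per arm = (z₁₋α + z₀.₈₀)² × [pC(1−pC) + pT(1−pT)] / (pT − pC + 0.07)²
= (1.645 + 0.842)² × (0.05375 + 0.0475) / 0.077²
= 6.183 × 0.10125 / 0.005929 = 105.6, so 106 per arm and 212 in total. This matches the plan, so the design does rest on the −0.07 null at one-sided 0.05.

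**2. The same formula at the level of a 95% CI.** With z = 1.960: 7.849 × 0.10125 / 0.005929 = 134.0, which rounds up to 135 per arm (270 in total) when z is not rounded. Approximate power at 106 per arm: SE = √(0.10125/106) = 0.0309 and 0.077/0.0309 = 2.491. Power is Φ(2.491 − 1.645) = 80% at one-sided 0.05 and Φ(2.491 − 1.960) = 70% at one-sided 0.025. At 110 per arm the figures are 81% and 72%.

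**3. What a non-significant p-value would be worth.** Exact enumeration of two binomials with L-PRF truly at the margin (0.943 − 0.07 = 0.873):

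| Result | 106 per arm | 110 per arm |
|---|---|---|
| t-test p ≥ 0.05 | 56% | 55% |
| Fisher p ≥ 0.05 | 66% | 64.5% |
| Wald 90% CI lower limit > −0.07 | 5.7% | 5.8% |
| Wald 95% CI lower limit > −0.07 | 3.1% | 3.1% |

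Example: 6 leaks among 106 controls and 14 among 106 L-PRF patients. The difference in success is −8/106 = −0.075, already beyond the margin, with Wald 95% CI −0.154 to 0.003. The t-test gives p = 0.061 and Fisher p = 0.098. An equality test is not significant here, while the comparison with −0.07 clearly fails.

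**4. Interval method.** Exact one-sided error at a true difference of −0.07, 110 per arm. The 95.9% row uses the 4.1% average leakage rate in Background and rationale {6a}.

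| Control success | Nominal | Wald | Score |
|---|---|---|---|
| 94.3% | 5% | 5.8% | 4.9% |
| 94.3% | 2.5% | 3.1% | 2.3% |
| 95.9% | 5% | 6.2% | 4.7% |
| 95.9% | 2.5% | 3.4% | 2.1% |

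**5. Exact power at the planning rates (95% against 94.3%).**

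| Rule | 106 per arm | 110 per arm |
|---|---|---|
| Wald, one-sided 0.05 | 80% | 82% |
| Wald, 95% CI | 72% | 73% |
| Score, one-sided 0.05 | 76% | 76% |
| Score, 95% CI | 64% | 63% |

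**The case against.** The strongest reply is that the plan already holds the parts. The Sample size section states the shifted hypothesis, its margin and its alpha as the hypothesis to be tested. The analysis section gives the primary outcome its own effect measure and interval, and a reader could compare that interval with −0.07. The t-test sentence does not name the primary outcome, and a null of zero is inferred from how such tests are usually run. A separate analysis plan may contain the rule, and the choice of interval method is commonly left to it.

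Much of this stands. A reader might infer that the −0.07 null is never tested, or that the trial will take non-significance as proof of non-inferiority. The documents support neither: the null is stated, a usable interval is promised, and nowhere is a non-significant p-value said to establish non-inferiority. The Wald method is likewise not named, and its excess error at the planned control rate is under one percentage point.

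What the reply does not remove is that the article is not silent here. It states a method, and that method does not fit the stated hypothesis. The opening sentence is not confined to secondary endpoints: they receive the same two tests again later in the paragraph, which would otherwise be redundant. The 95% CI does not settle the matter either, because no rule ties it to the margin and its level differs from the one used for sizing.

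**Conclusion.** The concern holds in this limited form: the analysis section does not carry the hypothesis of the Sample size section into a decision rule, its general test sentence does not suit the binary primary outcome, and its 95% CI implies one-sided 0.025 where the trial was sized at 0.05.

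- **Level mismatch.** Following the 95% CI as written, power at the planning rates is about 70–73% with a Wald-type interval, not 80%. This does not depend on any misreading.
- **Misread non-significance.** The 55–56% false-claim rate (t-test; 64.5–66% with Fisher) is conditional on taking p ≥ 0.05 as non-inferiority. It shows why the rule must be written down. It does not describe what the plan says it will do.
- **Wald interval.** If used, it is mildly liberal. This is a reason to prefer a score interval but is secondary.

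The figures assume the planned success rates, 106 or 110 analysed per arm and, for error rates, a true difference of exactly −0.07.

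**What to change.** For the primary outcome, replace the general sentence with a rule along these lines: estimate the L-PRF success proportion minus the control success proportion at 3 months, with a score interval (Miettinen–Nurminen or Farrington–Manning type), and conclude non-inferiority only if the lower limit exceeds −0.07. Keep the success scale throughout so that the sign is unambiguous. Limit the t-test and Mann–Whitney test to continuous secondary outcomes. If GraphPad Prism does not offer the interval, name free software that does.

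State one level:

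- a 90% CI, matching the one-sided 0.05 used for sizing; or
- a 95% CI, with power restated. By the plan's own formula, 80% power would then need 270 patients before drop-out.

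The text change is one paragraph, and it can be made before unblinding, since the article reports recruitment still open and plans no interim analysis. The real cost is power. With the score interval, exact power at the planning rates is about 76% at one-sided 0.05 and about 63–64% with a 95% CI, against the stated 80%. The sponsor should either report the lower figure or revisit the sample size.
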